### Assessment and analysis of secondary outcomes

The assessment and analysis of the secondary outcomes are described separately for each outcome.

#### Time to symptomatic gallstone disease

The time to symptomatic gallstone disease will be compared using Kaplan-Meier survival analysis. The outcome will be provided in the text.

#### The presence of gallstones/sludge in patients on ultrasound at 24 months

The date and result of the ultrasound at 24 months (window 18–30 months) will be recorded in a case report form. The numbers of patients in both study arms with ultrasounds performed and with gallstones at 24 months will be reported. The chi-squared test results and preferred measure for effect size will be shown in Table 2.

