## Summary study protocol

The UPGRADE trial is a randomised, placebo-controlled, double-blind multicentre trial comparing the prophylactic use of UDCA versus placebo in patients with morbid obesity undergoing bariatric surgery. Patients with an intact gallbladder and scheduled to undergo Roux-en-Y gastric bypass (RYGB) or sleeve gastrectomy (SG) were included. Patients were excluded in case of the existence of symptomatic gallstone disease prior to bariatric surgery, prior bariatric surgery, prior gallbladder surgery, inflammatory bowel disease and other conditions of the small intestine and liver which may interfere with enterohepatic circulation of bile salts, hypersensitivity to ingredients of UDCA or placebo, and intake of UDCA within the last 30 days before screening. Patients were randomly assigned to either UDCA 900 mg daily for 6 months or placebo in a 1:1 ratio. Randomisation was done prior to surgery with an online computer software program (ALEA AMC, Amsterdam, the Netherlands, version 2.2) and implemented into a web-based application. Randomisation was stratified for the presence of gallstones (yes versus no) and type of surgery (RYGB versus SG) and performed by using random block sizes of 4, 6 and 8. Data are collected during hospitalisation and study visits at 6 weeks (window 4–8 weeks) and 16 weeks (window 14–18 weeks) and at 6 months (window 5–9 months), 12 months (window 10–15 months) and 24 months (window 24–30 months) by standardised case report forms. Questionnaires are gathered at baseline, 6 weeks, and 3, 6, 12, 18 and 24 months (windows 1 week before to 2 weeks after the date of administration). The primary outcome is symptomatic gallstone disease within 24 months, defined as admission or hospital visit for symptomatic gallstone disease. Secondary outcomes consist of the development of gallstones/sludge on ultrasound at 24 months in the gallstone-negative group at baseline (window 18–30 months), presence of gallstones/sludge on ultrasound at 24 months (window 18–30 months), number of cholecystectomies, time to symptomatic gallstone disease and cholecystectomy, side effects of UDCA, therapy compliance, quality of life, costs and revenues. Safety outcomes are adverse events (AEs), serious adverse events (SAEs) and suspected unexpected serious adverse reactions (SUSARs). For the sample size calculation, we refer to the study protocol [4]. On 22 October 2018, all included patients underwent surgery, and complete 2-year follow-up data are expected in November 2020. For the complete study protocol, we refer to the previous publication [4].

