## Statistical analysis plan

### General principles

The randomisation code will not be broken until the last patient reaches 24 months of follow-up, all primary endpoints are reviewed by a blinded independent endpoint adjudication committee, and data cleaning is completed. The analyses will be performed after data verification and validation have been carried out and after this SAP has been accepted for publication. Analyses will be done by the investigators and biostatistician of the UPGRADE study group, using the most recent version of the SPSS statistical software at the time of analysis. All statistical tests will use a two-sided *p* value of 0.05, and two-sided 95% confidence intervals will be presented for all estimates.

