## Discussion

The aim of the UPGRADE trial is to provide evidence regarding the prophylactic use of UDCA in preventing symptomatic gallstone disease after bariatric surgery. This SAP describes the analyses to be published in the primary paper. By publishing this SAP before the data are available, we stimulate transparency of scientific conduct and support reproducibility, thereby allowing others to review our plans.

Randomisation in the UPGRADE trial was stratified for the presence of gallstones. Approximately 20% of patients undergoing bariatric surgery already have asymptomatic gallstones [10]. The majority of earlier performed studies excluded these patients, but we decided to include them because they receive no other or extra treatment after surgery in the current practice. If these patients have a higher risk of becoming symptomatic after surgery, they will be distributed equally over the two study arms.

After adding SG to the inclusion criteria, randomisation was also stratified for the type of surgery. Due to this addition, external validity was increased and internal validity was ensured by incorporating ‘type of surgery’ as a stratification factor. Although the mechanisms of weight loss differ between RYGB and SG, similar percentages of gallstone disease have been reported [11]. To conform to the guidelines of Good Clinical Practice, we decided that patients—who did undergo SG before the protocol amendment was approved—were excluded from the trial and did not receive trial medication. Furthermore, the conduct of the trial forced us to perform the stratified randomisation before the patient underwent surgery. Consequently, a minority of patients was allocated to the wrong type of surgery. Most of them received a SG instead of a RYGB, because the RYGB was technically not possible. These patients will be excluded from the PPSs, because of a protocol deviation.

In our trial, patients were not monitored and cared for more considerately than patients treated outside the trial. Furthermore, we did not stimulate therapy compliance by frequent positive enforcement, because we aimed to provide a realistic manifestation of daily clinical practice. However, we did decide to extend the period in which patients had to start with the trial medication, from 2 weeks to a maximum of 8 weeks after surgery during the course of the trial. We will investigate whether the timing of the start of the trial medication influences the efficacy of UDCA.

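### Presence of gallstones/sludge at 24 months is tested without its own baseline value; stratifying by baseline gallstones is a free gain in precision for this one secondary outcome

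*SAP article*

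**What the plan says.** The SAP article, section *The presence of gallstones/sludge in patients on ultrasound at 24 months*, states: "The numbers of patients in both study arms with ultrasounds performed and with gallstones at 24 months will be reported". It continues: "The chi-squared test results and preferred measure for effect size will be shown in Table 2". The section names no covariate, no stratification and no restriction by baseline stones.

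Baseline stone status is already held. *Summary study protocol* says "Randomisation was stratified for the presence of gallstones (yes versus no) and type of surgery (RYGB versus SG"), and preoperative cholecystolithiasis is a row of Table 1. The *Discussion* gives an expected prevalence: "Approximately 20% of patients undergoing bariatric surgery already have asymptomatic gallstones".

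Four neighbouring provisions matter:
- The next section, on newly formed gallstones/sludge, plans a separate chi-squared test in patients without stones at baseline.
- *Quality of life and health utility* adjusts follow-up utility for its baseline value.
- *Additional analyses* uses the stratification factors only in an exploratory interaction model.
- *Patient replacement and handling of missing data* treats the ultrasound of patients reached only by telephone as missing, and plans multiple imputation.

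**The concern.** Baseline stone status is not merely a risk factor for this outcome; it is the same variable measured earlier. A pooled comparison counts between-stratum variation (patients with old stones against patients without) as noise. Stratified allocation has largely removed that variation from the treatment contrast, so the ordinary chi-squared variance is too large. The test then rejects less often than its nominal level under the null and has less power under an effect.

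The comparison is also made in scanned patients. Balance at randomisation does not guarantee balance in that subset, and a pooled test has no means of correcting a chance difference.

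What is at stake is the precision and readability of one named row of Table 2 with its own p value.

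**Working it through.** The SAP states no power or rates for this outcome, so there is no plan figure to reproduce. For the sample size it says "For the sample size calculation, we refer to the study protocol [4".

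**Inputs from the SAP:** two-sided 0.05; 1:1 allocation; about 20% with baseline stones.

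**Assumed inputs, central case:** 300 scanned per arm; 90% of baseline stones still present at 24 months in both arms; new stones 20% on placebo v 10% on UDCA; baseline strata balanced, so 240 negative and 60 positive per arm.

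**Pooled risks**
- Placebo: 0.8×0.20 + 0.2×0.90 = 0.34
- UDCA: 0.8×0.10 + 0.2×0.90 = 0.26
- Difference d = 0.08; risk ratio 0.26/0.34 = 0.76; mean risk 0.30

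**Standard errors**
- Crude null SE: √(2×0.30×0.70/300) = 0.0374
- Stratified null SE: √[(0.8×2×0.15×0.85 + 0.2×2×0.90×0.10)/300] = √(0.240/300) = 0.0283
- True SE of d under balanced strata: √[(0.8×(0.16+0.09) + 0.2×(0.09+0.09))/300] = √(0.236/300) = 0.0280

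The variance used by the test falls from 0.420/300 to 0.240/300, a cut of 43%.

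**Power** = Φ[(d − 1.96×null SE)/true SE]
- Crude: Φ[(0.08 − 0.0733)/0.0280] = 59%
- Stratified: Φ[(0.08 − 0.0554)/0.0280] = 81%
- Gain: about 22 points. Simulation agrees (59% v 81%).

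**Type I error.** With 20% new stones in both arms, the pooled risk is 0.34. The crude variance term is 2×0.34×0.66 = 0.449; the true one is 2×(0.8×0.16 + 0.2×0.09) = 0.292. The effective critical value is 1.96×√(0.449/0.292) = 2.43, so the crude test rejects in about 1.5% of trials instead of 5%. The stratified test rejects in 5.0% by simulation. If strata sizes vary by chance, the crude test is back near 5% (4.9% by simulation) but still has lower power (57% v 81% in the central case).

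**Dependence on persistence** (other central inputs unchanged)

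| Persistence | Crude | Stratified | Gain (points) |
|---|---|---|---|
| 95% | 59% | 84% | 25 |
| 90% | 59% | 81% | 22 |
| 80% | 61% | 77% | 16 |
| 70% | 63% | 73% | 11 |
| 60% | 65% | 72% | 7 |
| 50% | 67% | 71% | 4 |

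**Grid.** 72 settings with 20% baseline stones: 200, 300 or 400 per arm; persistence 80, 90 or 95%; placebo new-stone risk 15, 20, 25 or 30%; risk ratio for new stones 0.5 or 0.6.
- The gain runs from about 2 points (400 per arm, 80% persistence, 30% v 15%: 97.0% v 98.5%) to 38 (300 per arm, 95% persistence, 15% v 7.5%: 31% v 69%).
- By these formulas 15 settings lie below 10 points and 16 above 25.
- Small gains are not confined to very high crude power: 300 per arm, 80% persistence, 30% v 18% gives 72% v 80%.

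**Chance imbalance.** If baseline stones were 18% on UDCA and 22% on placebo among scanned patients, with no drug effect, the crude risk ratio would be (0.18×0.9 + 0.82×0.2)/(0.22×0.9 + 0.78×0.2) = 0.326/0.354 = 0.92.

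**What stratification leaves unchanged.** With equal strata sizes the Mantel-Haenszel risk ratio is (54+24)/(54+48) = 78/102 = 0.76, the same as the crude one.

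**The case against.** The strongest reply is the planned test of newly formed stones in baseline-negative patients. Persisting stones cannot enter it. In the central case it has 240 per arm at 20% v 10%, and power Φ[(0.10 − 1.96×0.0326)/0.0323] = 87%, above the 81% of the stratified all-patients test. It was ahead in all 72 settings. A reader might infer that the trial is likely to miss a real effect on stones, or that old stones swamp the ultrasound contrast. The documents do not support either reading. What remains is narrower: the all-patients outcome is listed and tested separately, and the new-stones test does not make its p value any better. The ranking also depends on the assumption that UDCA leaves existing stones alone. With 300 per arm, 20% v 14% new stones and persistence 90% v 80%, the same formulas give crude 42%, new-stones test 42% and stratified 61%.

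Second, stratification does not cure dilution. The all-patients risk ratio stays near 0.76 when the ratio for new stones is 0.50, because dilution belongs to the outcome and not to the test. This stands in full; only counts by baseline status make it visible.

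Third, persistence is not stated anywhere. Some baseline-positive patients may have had a cholecystectomy by 24 months. It would be tempting to treat them as near-certain positives and quote a fixed loss such as 10 to 25 points; neither can be derived from the SAP.

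Fourth, a marked imbalance is unlikely. The trial is blinded, and centre bankruptcy and COVID-19 are not related to arm. If 25% of scans were missing at random from 400 per arm (assumed), 18% v 22% among the 300 scanned would be a 2.4 SD event. So this is protection against chance, not a demonstrated bias. Multiple imputation could draw on baseline stones, but it would not change the unstratified test.

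Finally, the crude test does not inflate false positives. That also stands.

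**Conclusion.** The point holds as an efficiency and robustness weakness in one secondary outcome. The planned test is valid, but it leaves unused a baseline value that is the outcome's own earlier measurement and a randomisation stratum. With balanced strata it rejects about 1.5% of the time under the null in the case worked above.

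The power loss is about 22 points in the central case and about 2 to 38 points over the grid, falling to about 4 points if persistence were 50%. Apart from the 20% prevalence, the 1:1 allocation and the 5% level, every input is an assumption.

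The primary outcome and the new-stones comparison are unaffected. Label: free improvement.

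**What to change.** In the section on presence of gallstones/sludge at 24 months, before the randomisation code is broken:

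1. Replace the unstratified chi-squared test with a Cochran-Mantel-Haenszel test stratified by baseline gallstones (yes/no).
2. Report a stratified risk difference or risk ratio with its 95% confidence interval. The risk difference is Σw·d/Σw over the two strata, with w = n₁n₀/(n₁+n₀). In the central case this is (120×0.10 + 30×0)/150 = 0.08. It reads more easily than a common ratio if the ratio differs between strata.
3. Report 24-month counts by arm for baseline-positive patients beside the baseline-negative counts already planned, so that persistence and formation can be told apart. The crude percentages can stay in Table 2 as description.

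The cost is a sentence or two in the SAP and one extra pair of counts. No new data are needed, since baseline gallstone status was required for randomisation.

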### Assessment and analysis of primary outcome

The primary outcome is the proportion of patients with symptomatic gallstone disease within 24 months of follow-up. Symptomatic gallstone disease is defined as a biliary disease (biliary pancreatitis, acute cholecystitis, choledocholithiasis, cholangitis or biliary colics) for which a hospital visit or admission was required. To assess the primary outcome, follow-up appointments are held at 6 and 16 weeks, and 6, 12 and 24 months by one of the blinded investigators. All primary endpoints will be reviewed by a blinded independent endpoint adjudication committee.

To provide an estimator of the effectiveness of UDCA, we will perform a standard ITT analysis. The difference between outcomes by study arm will be compared using the chi-squared test with a risk ratio (unless editors of the accepting journal suggest to report odds ratio) as an indicator for effect size, as shown in Table 2. The results of the mITT and other data sets will be provided in a supplementary appendix, if no contradictory findings are to be reported.

**Table 2 Tab2:** Gallstone-related outcomes

	UDCA (***n***=)	Placebo (***n***=)	Effect size	***p***
*Primary outcome*				
**Symptomatic gallstone disease**—*n* (% *n*/*N*)				
Biliary pancreatitis				
Acute cholecystitis				
Choledocholithiasis				
Cholangitis				
Biliary colic				
*Secondary outcomes*				
**Presence of gallstones/sludge on ultrasound at 24 months**—*n* (% *n*/*N*)				
**Newly formed gallstones/sludge on ultrasound at 24 months**—*n* (% *n*/*N*)				
**Cholecystectomy**—*n* (% *n*/*N*)				

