#### Newly formed gallstones/sludge on ultrasound in patients on ultrasound at 24 months

In patients without gallstones at baseline, the total number of patients with newly formed gallstones on ultrasound at 24 months will be reported. The chi-squared test results and preferred measure for effect size will be shown in Table 2.

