#### The number of and time to cholecystectomies

The total number of patients with cholecystectomies in both study arms will be reported. Whether a patient underwent a cholecystectomy is registered by an investigator in the case report form and verified at the 24-month follow-up. The chi-squared test will be used to compare the outcomes between the study arms. The time to cholecystectomy will be compared using Kaplan-Meier survival analysis. The number of cholecystectomies and preferred effect size will be shown in Table 2, and the outcome of the Kaplan-Meier survival will be provided in the text.

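### The 24-month ultrasound outcomes have no rule for patients whose gallbladder was removed before the scan, and sludge is defined inconsistently; this should be fixed, for secondary outcomes only

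*SAP article*

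**What the plan says.** The SAP article gives two imaging outcomes among its secondary outcomes. The section on presence of gallstones/sludge at 24 months states that "The numbers of patients in both study arms with ultrasounds performed and with gallstones at 24 months will be reported". The section on newly formed gallstones/sludge states: "In patients without gallstones at baseline, the total number of patients with newly formed gallstones on ultrasound at 24 months will be reported". Both use the scan in the 18–30 month window, a chi-squared test and the preferred effect measure, which the primary outcome section gives as the risk ratio unless a journal asks for the odds ratio.

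Every patient starts with a gallbladder: "Patients with an intact gallbladder and scheduled to undergo Roux-en-Y gastric bypass (RYGB) or sleeve gastrectomy (SG) were included". Removal during follow-up is a secondary outcome of its own: "The total number of patients with cholecystectomies in both study arms will be reported". The SAP does not link that outcome to the imaging outcomes.

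*Patient replacement and handling of missing data* treats the scan as missing for patients followed by telephone and for those who cannot be contacted. Multiple imputation is then to be chosen at the time of analysis, with none below 2% missing. The best- and worst-case scenario there concerns symptomatic disease only.

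On sludge, *Summary study protocol* lists "the development of gallstones/sludge on ultrasound at 24 months in the gallstone-negative group at baseline", and Table 2 has the row "Newly formed gallstones/sludge on ultrasound at 24 months". The two operative sentences name gallstones only. So do the baseline restriction and the stratification factor.

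**The concern.** A patient who forms stones after bariatric surgery and has the gallbladder removed before the scan is a clear case of stone formation. A gallbladder scan at 24 months cannot show it. The plan gives this patient no status, so the analyst must choose between three routes: scanned and negative, dropped as unscanned, or imputed from patients who still have a gallbladder. Each discards what is known about the patient.

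The loss occurs after randomisation and can be caused by the outcome itself. If UDCA works as the trial hopes, it will also differ by arm. The newly formed outcome suffers most, because its aim is to count new stones over follow-up.

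Sludge is a second gap in the same definitions. If it counts at 24 months but not at baseline, sludge already present at entry can appear as newly formed. If it does not count, the headings and Table 2 carry the wrong label.

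**Working it through.** The SAP states no expected stone rate, scan number or power for these outcomes, so there is no figure to reproduce. The check is illustrative arithmetic.

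**Notation.** S is the share who ever form stones and C the share with cholecystectomy for stones before the scan, each by arm (P placebo, U UDCA).

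- All formers counted: rate S.
- Operated patients counted negative: rate S − C.
- Operated patients dropped: rate (S − C)/(1 − C). Imputing from scanned patients of the same arm, with no other predictor, gives the same expected rate.

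**Direction.** Counted negative, the absolute difference shrinks by exactly C_P − C_U. The risk ratio becomes (S_U − C_U)/(S_P − C_P). This equals the true ratio only if C and S fall by the same proportion. It moves towards 1 if cholecystectomy falls proportionally more than stones, and away from 1 if it falls less.

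**Inputs.** The stone rates are assumptions throughout, as are the cholecystectomy rates in rows 1–3. Rows 4 and 5 use the document's 8–15% symptomatic disease (Abstract, Background) as the placebo rate and the 50% reduction used in the power analysis (Discussion). They also assume that every symptomatic patient is operated on before the scan, which is an extreme, and that the 8–15% applies to the patients analysed.

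| Row | Stones, P vs U | Cholecystectomy, P vs U | All counted: RR; difference | Counted negative | Dropped |
|---|---|---|---|---|---|
| 1 | 40% vs 30% | 12% vs 6% | 0.75; 10.0 points | 28.0% vs 24.0%: 0.86; 4.0 | 31.8% vs 25.5%: 0.80; 6.3 |
| 2 | 30% vs 15% | 10% vs 5% | 0.50; 15.0 | 20.0% vs 10.0%: 0.50; 10.0 | 22.2% vs 10.5%: 0.47; 11.7 |
| 3 | 30% vs 15% | 8% vs 8% | 0.50; 15.0 | 22.0% vs 7.0%: 0.32; 15.0 | 23.9% vs 7.6%: 0.32; 16.3 |
| 4 | 30% vs 20% | 8% vs 4% | 0.67; 10.0 | 22.0% vs 16.0%: 0.73; 6.0 | 23.9% vs 16.7%: 0.70; 7.2 |
| 5 | 30% vs 20% | 15% vs 7.5% | 0.67; 10.0 | 15.0% vs 12.5%: 0.83; 2.5 | 17.6% vs 13.5%: 0.77; 4.1 |

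Worked for row 1, dropped: (0.40 − 0.12)/(1 − 0.12) = 0.318 and (0.30 − 0.06)/(1 − 0.06) = 0.255, ratio 0.80.

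**Sludge.** Suppose a share s has baseline sludge that persists, equal in both arms, and is counted as new. The observed rate is s + (1 − s)S. With S of 30% vs 15% (true ratio 0.50):

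- s = 2%: 31.4% vs 16.7%, ratio 0.53.
- s = 5%: 33.5% vs 19.25%, ratio 0.57 (0.575 before rounding).
- s = 10%: 37.0% vs 23.5%, ratio 0.64 (0.635 before rounding).

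The values of s are assumptions. The dilution arises only if sludge counts at 24 months and sludge alone at baseline was not classed as gallstones.

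**The case against.** **The plan is silent, not wrong.** A reader might infer that the SAP makes operated patients stone-free or missing, or that it imputes a scan for an absent gallbladder. It says neither. The missing-data section names only patients followed by telephone or not reached, and leaves the imputation method open. The protocol, which is not shown, may hold a rule. This stands against any claim of a stated error. It does not remove the gap, because the SAP itself sets out how these two outcomes are counted, and every open route loses the known stone formers.

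**Presence at 24 months is a point prevalence.** A patient without a gallbladder is not simply misclassified by it, and the set includes patients with stones at entry (approximately 20% of bariatric patients, Discussion). This stands. The formation argument belongs mainly to the newly formed outcome.

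**The effect need not be dilution.** This also stands: row 2 leaves the planned risk ratio at 0.50 when operated patients count as negative, and row 3 exaggerates it. That the effect always shrinks is a tempting reading which the arithmetic refutes.

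**Sludge may be mere shorthand.** The Abstract, *Summary study protocol*, both headings and Table 2 all include it, so the gallstones-only sentences may be loose wording. If they are meant literally, baseline sludge cannot become a new event. The mismatch is real, but its numerical effect is conditional.

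**The damage is partly visible.** Scans performed will be reported by arm, and cholecystectomies by arm appear in Table 2. That would reveal unequal removal without correcting the comparison.

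**Conclusion.** The point holds as one that should be fixed; it does not threaten the trial's main conclusion. The primary outcome is clinical, is adjudicated and does not depend on the scan.

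The ultrasound outcomes lack a rule for cholecystectomy before the scan, and this matters most for newly formed gallstones/sludge. Size and direction rest on rates the document does not give. In the illustrations, counting operated patients as negative or dropping them moves the risk ratio from 0.75 to 0.86 or 0.80 (row 1), leaves it at 0.50 or moves it to 0.47 (row 2), or overstates benefit at 0.32 (row 3). An unknown direction is itself a reason to fix the rule before the code is broken.

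On sludge, the definition is inconsistent within the SAP and must be reconciled. A reader might conclude that prevalent sludge will be counted as new. The document does not establish that, because it does not say how baseline sludge was classified.

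**What to change.** Settle the following in the SAP before unblinding.

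1. **Newly formed outcome.** In baseline-negative patients, count cholecystectomy for gallstone disease before the scan, or adjudicated symptomatic gallstone disease leading to it, as an event. Keep the scan-only count as a sensitivity analysis.
2. **Presence outcome.** Report the number without a gallbladder in each arm and do not impute scans for them. Alongside the scan-only prevalence, give the composite of stones or sludge on the scan or prior cholecystectomy for gallstone disease.
3. **Sludge.** Use gallstones/sludge in both operative sentences and apply the same definition at baseline and at 24 months. If baseline sludge was not recorded, make the newly formed outcome gallstones only, or report it that way as a sensitivity analysis.

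The cost is mainly wording. Cholecystectomy is already on the case report form, and symptomatic events are already adjudicated. The SAP does not show that stones found at operation or baseline sludge were recorded, so the rule above relies on gallstone disease as the reason for surgery, which should be checked against the forms. The downside is that the newly formed outcome is no longer purely ultrasound-based and overlaps with the clinical outcomes; the scan-only analysis keeps the imaging result visible.
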